## Abstract

**Background:**

Whereas ultra-short stay (day care or 24 hour hospitalisation) following breast cancer surgery was introduced in the US and Canada in the 1990s, it is not yet common practice in Europe. This paper describes the design of the MaDO study, which involves the implementation of ultra short stay admission for patients after breast cancer surgery, and evaluates whether the targets of the implementation strategy are reached. The ultra short stay programme and the applied implementation strategy will be evaluated from the economic perspective.

**Methods/design:**

The MaDO study is a pre-post-controlled multi-centre study, that is performed in four hospitals in the Netherlands. It includes a pre and post measuring period of six months each with six months of implementation in between in at least 40 patients per hospital per measurement period.

Primary outcome measure is the percentage of patients treated in ultra short stay. Secondary endpoints are the percentage of patients treated according to protocol, degree of involvement of home care nursing, quality of care from the patient's perspective, cost-effectiveness of the ultra short stay programme and cost-effectiveness of the implementation strategy. Quality of care will be measured by the QUOTE-breast cancer instrument, cost-effectiveness of the ultra short stay programme will be measured by means of the EuroQol (administered at four time-points) and a cost book for patients. Cost-effectiveness analysis will be performed from a societal perspective. Cost-effectiveness of the implementation strategy will be measured by determination of the costs of implementation activities.

**Discussion:**

This study will reveal barriers and facilitators for implementation of the ultra short stay programme. Moreover, the results of the study will provide information about the cost-effectiveness of the ultra short stay programme and the implementation strategy.

**Trial registration:**

Current Controlled Trials ISRCTN77253391.

## Background

Opinions on more optimal working methods ('best practice') for breast cancer treatment have been changing continuously[1-6]. Increasingly, implementation studies are applied investigating techniques how to change clinical practice to integrate 'best practice' recommendations[7,8]. Whether a new programme is consolidated after implementation depends on the quality of care, the cost-effectiveness of the innovation as such, and of the cost-effectiveness of the innovation incorporating the costs of implementation[9].

Breast cancer causes a prominent burden on the health care budget. Of the total costs of breast cancer treatment 35–50%[10] is spent on surgical treatment, of which the largest part is on account of the hospital stay. Since the 1990s, hospital stay has decreased from 10–14 days to 5–7 days and further to the level of day care admission[11-15]. Three randomised clinical trials on the subject of early discharge (2–4 days vs. 5–10 days) reported no adverse effects and lower illness rates, high patient satisfaction and good clinical outcomes for the early discharge as compared to the standard admission group[16-18].

A decrease in admission time should not affect quality of care in a negative way. Therefore, it is important to introduce a structured programme such as has been developed at University Hospital Maastricht (uhM) that includes current quality of care criteria[4,5,19]. Moreover, criteria for education, support and evaluation of the breast cancer care programme can (provide information to) enhance quality of care. Measurement of quality of care is of fundamental importance when evaluating a new programme.

At the uhM, an ultra short stay programme for breast cancer surgery was developed and evaluated, incorporating the aspects mentioned above. The programme consists of a structured care organisation including education and counselling, dedicated anaesthesia, active participation of the patient in her own treatment plan and in the decision to go home, and home care nursing. NABON guideline quality indicators are also incorporated in the programme (e.g. access time for the first visit to the Breast Unit, time spent in the process, number of breast conserving procedures and all diagnostic and treatment decisions being made in an appropriate multidisciplinary setting)[19]. Although the uhM programme was successful in the end, the programme was greeted with scepticism by both health care providers and members of the local breast cancer patient association. For example, in the beginning patients were discouraged by ward nurses to go home in the evening following surgery for the nurses did not trust the quality of the programme at that moment. In addition, it suffered from problems at the anaesthesiology department (e.g. administration of opioids at the recovery unit postoperatively even if patients did not suffer pain) and from organisational flaws. For instance, the day care surgery unit closed at 1800 hours and, therefore, patients operated on late in the afternoon had less recovery time as compared to those operated on early in the morning. Following on those limited opening hours, patients in need of more time to recover after 1800 hours were transferred to the inpatient ward from which discharge the same evening was rarely performed.

Traditionally, implementation strategies have been chosen for pragmatic reasons guided by personal acquaintance with a particular strategy[20]. In this project we chose to perform an extensive diagnostic analysis[20] of the problem, consisting of three issues:

1) how is current care organised?

2) how does it deviate from optimal care according to the innovative care programme?

3) what are barriers and facilitators for implementation of the ultra short stay programme?

The uhM experience accumulated valuable insight and knowledge about implementation of an ultra short stay programme for breast cancer. If such a programme is implemented on a wider scale, in other hospitals, these experiences may contribute to the design of implementation strategies that are tailored to local needs.

The implementation strategy will be developed on the basis of the results of the diagnostic problem analyses, and tailored to the needs of the stakeholder groups. The insights generated from this study may be translated into generally applicable insights on implementation of the innovative care programme on a larger scale while again defining patient benefits and demonstrating cost containment through the type of care provided.

### Aim and objectives

#### Aim

The aim of this study is to implement a programme incorporating breast cancer surgery in an ambulatory/24 hour stay setting, (tailored to the needs of these hospitals).

#### Objectives

To evaluate:

1) whether the percentage of patients treated in ultra short stay increases without an increase in the number of complications.

2) whether the quality of care as perceived by patients between the baseline measurement and measurement after implementation does not deteriorate.

3) the cost-effectiveness of the ultra short stay programme versus care as usual (programme cost-effectiveness) in the baseline period.

4) the cost-effectiveness of implementation of the ultra short stay programme versus 'doing nothing' (policy cost-effectiveness).

5) the actual performance of the professionals in the test hospitals according to performance indicators.

6) the perceived barriers and facilitators for the implementation of the programme incorporating surgery in ambulatory/24 hour stay setting in the participating hospitals so others preparing to change to ultra short stay care can profit from this information.

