### Sample size calculations

In the uhM the percentage of patients discharged within 24 hours has increased from 13% to 84%. Our assumption is that the clinically significant difference of ultra short stay admissions between the pre and post measurement is at least 30% in all participating hospitals. To achieve this percentage, 40 patients are sufficient for both the pre and the post measurement in each of the hospitals to demonstrate statistical relevance (p < 0.05) with a power of 0.90[22].

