### Statistical analyses

Intention to treat will be used for data analyses, and analyses will be performed using the SPSS package, version 12.0.1 ^® ^for Windows (SPSS INC 1989–2003). P values < 0.05 will be defined as statistically significant. The pre and post comparison of the interval scaled outcome variables will be analysed with a multivariate linear regression model. Apart from the independent variable hospital, other independent variables included in this model are type of surgery, age, informal care at home, involvement of home care nursing and starting time of surgery. Furthermore, correlation of data within a hospital are accounted for by clustered data analysis.

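### The two absence-of-harm objectives (complications, perceived quality) are paired only with a p<0.05 criterion and a sample size set for short stay, neither of which can establish absence of harm

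*Protocol article*

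**What the plan says.** Under Objectives, the first item is to evaluate "whether the percentage of patients treated in ultra short stay increases without an increase in the number of complications". The second is to evaluate "whether the quality of care as perceived by patients between the baseline measurement and measurement after implementation does not deteriorate". Both ask whether something bad does not happen.

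Under Statistical analyses, the one inferential criterion is "P values < 0.05 will be defined as statistically significant". The only model described there is for interval-scaled data: "The pre and post comparison of the interval scaled outcome variables will be analysed with a multivariate linear regression model". It is adjusted for hospital and other covariates, with clustering within hospital taken into account.

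Under Sample size calculations, the basis is that "the clinically significant difference of ultra short stay admissions between the pre and post measurement is at least 30% in all participating hospitals". From this comes 40 patients per hospital per period "with a power of 0.90". The Discussion adds a general statement that numbers across the four hospitals are adequate for estimating change. It does not mention complications or quality.

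The article gives no margin, tolerable increase, confidence-limit rule, expected complication rate, or power for complications or the QUOTE score.

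**The concern.** A test of difference can show that complications rose. It cannot show that they did not, because a non-significant result is also what a small or noisy study produces when harm is real. If such results were taken as meeting objectives 1 and 2, fewer patients would make the reassuring answer easier to reach.

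Objective 1 ties the success of the programme to safety, and the Background looks ahead to wider implementation. A statement that complications did not rise, or that quality held up, would carry weight in that decision. The printed criterion and sample-size basis do not equip the study to make it.

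**Working it through.** **The plan's own figure.** The 40 per period per hospital is for a 30-point rise in short stay. The planning baseline is not stated, so it can be checked only conditionally. The usual two-proportion formula, two-sided 5% and 90% power, is n = [1.96·√(2p̄(1−p̄)) + 1.2816·√(p1(1−p1)+p2(1−p2))]² / δ².
- 5% to 35%: n = 36
- 10% to 40%: n = (1.200 + 0.736)² / 0.09 = 41.7, so 42
- 13% to 43%: n = 45

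So 40 is reachable with a baseline near 10%. It says nothing about complications or quality.

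**Inputs for the check.** Four hospitals (Selection of hospitals) × 40 (Sample size calculations) = 160 per period, which is a minimum. Alpha is 0.05; sidedness is not stated and two-sided is used. Complication rates of 5%, 10%, 20% and 30% are assumptions. Clustering is ignored.

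**Chance that a real rise is significant.** Power = Φ{[δ√n − 1.96·√(2p̄(1−p̄))] / √(p1(1−p1)+p2(1−p2))}.

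Example, 10% to 15%, n = 160: (0.05 × 12.649 − 1.96 × 0.4677) / 0.4664 = (0.632 − 0.917) / 0.4664 = −0.61, so power is 0.27.

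| Assumed baseline | 5-point rise: power (non-significant) | 10-point rise: power (non-significant) | 95% CI half-width, equal rates |
|---|---|---|---|
| 5% | 0.40 (60%) | 0.85 (15%) | 4.8 points |
| 10% | 0.27 (73%) | 0.71 (29%) | 6.6 points |
| 20% | 0.19 (81%) | 0.54 (46%) | 8.8 points |
| 30% | 0.16 (84%) | 0.47 (53%) | 10.0 points |

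The half-width is 1.96·√(2p(1−p)/160); at 10%, 1.96 × 0.0335 = 0.066.

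**What 160 per period could exclude.** With equal true rates, the margin that the upper 95% limit excludes with 90% power is (1.96 + 1.28)·√(2p(1−p)/160):
- rate 5%: 3.24 × 0.0244 = 0.079, about 8 points
- rate 10%: 3.24 × 0.0335 = 0.109, about 11 points
- rate 20%: 3.24 × 0.0447 = 0.145, about 14.5 points

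**Quality score, in SD units.** Power at 160 per period is Φ(d·√80 − 1.96). A loss of 0.2 SD gives Φ(1.79 − 1.96) = 0.43, and a loss of 0.3 SD gives 0.77. A 0.2 SD loss would thus be non-significant in about 57% of studies.

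**The case against.** The strongest reply is that the misuse is inferred. A reader might take the plan to say that p≥0.05 counts as safety. It does not: the article defines what is significant and is silent on how a non-significant result will be read, and the objectives are posed as questions. Nor is any test named for complications, since the regression covers interval-scaled outcomes only. That model would yield an estimate and interval for quality, and nothing forbids reporting it. A margin could sit in a fuller document not shown. All this stands. What remains is that the criterion and sample-size basis that are printed cannot answer two objectives that are also printed.

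The size of the problem is also open to challenge. Every complication rate is assumed, and 160 is a floor: the Abstract says at least 40 per hospital per period, and Inclusion criteria take all consecutive patients. At an assumed 320 per period, power for 10% to 15% would be about 0.48 instead of 0.27. At a 5% rate and a 10-point margin, 160 per period would give power of 0.98 to exclude the margin. These points limit the magnitude, but a non-significant result would still not show absence of harm.

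A reader might also conclude that most studies of this size would miss any substantial rise. The figures do not support that: a rise from 10% to 20% is detected in about 71%, and one from 5% to 15% in about 85%. Nor does the word number in objective 1 show that raw counts will be compared across periods of different size, because Table 2 lists the complication rate as the indicator.

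Finally, short stay is the primary outcome, and sizing a study for its primary outcome is normal. That bears on severity.

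**Conclusion.** The point holds as a mismatch between objectives and method. Objectives 1 (its complications part) and 2 ask about absence of harm, while the stated criterion and sample size are built to detect a difference. A non-significant comparison could not support either objective, however the authors intend to read it.

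The size is conditional. At the minimum 160 per period, a true 5-point rise in complications would be non-significant in roughly 60% to 84% of studies over assumed baselines of 5% to 30%. These figures rest on assumed rates, a two-sided test and independent patients. Hospitals differing in their pre-post change would reduce power; enrolment above the minimum would raise it. Severity is moderate: these outcomes are not primary, and the remedy lies in the analysis rule and the wording of conclusions.

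**What to change.** For objectives 1 (complications) and 2, replace reliance on p<0.05 with the two-sided 95% confidence interval for post minus pre, allowing for hospital clustering:

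- **Complications:** the difference in the proportion of patients with at least one complication, judged by the upper limit.
- **Quality:** the difference in the QUOTE score, judged by the limit on the side of worse quality.

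Conclude absence of an increase or of deterioration only if that limit excludes a margin fixed before the post period starts. Otherwise report the interval and call the result inconclusive. If the protocol states what margin the study can exclude (about 8, 11 and 14.5 points with 90% power at rates of 5%, 10% and 20%), it should label those figures as conditional on the assumed rate and on 160 per period, and as ignoring clustering.

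The cost is a change of wording and agreement by the study team on two margins; no extra patients are needed. The real downside is that the safety claim becomes harder to make, and the study may end with an inconclusive finding on complications.

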## Methods/Design

### Study design

The MaDO study is a multi-centre pre-post uncontrolled prospective study and involves breast cancer patients who are operated on with curative intent. Both pre and post- measurements last six months with an implementation period of six months in between.

### Selection of hospitals

The study is performed in four hospitals which have been selected on three criteria. First, all participating hospitals had to be recognised as early adopters (an active group with high status within the target group)[21] within the field of breast cancer treatment, expressed by the willingness to appoint a full-time breast nurse. Second, we wished to include one university hospital, one large training hospital, one small training hospital and one non-training hospital to cover the main organisational hospital settings in the Netherlands, and to assess whether difference in results could be explained by differences in setting. Third, recruitment of people from different hospitals from different parts in the Netherlands, enables us to have a representative sample of breast cancer patients in the Netherlands

### Selection of patients

#### Inclusion criteria

All consecutive patients from the four participating hospitals, aged over 17 years, diagnosed with breast cancer, and scheduled to undergo surgery are eligible for participation in the study.

#### Exclusion criteria

Concerning surgical techniques, there is no contra-indication for ultra-short stay. Patients whose physiology impedes participation, as assessed by the breast surgeon and breast nurse, are excluded from the study. Patients who cannot rely on sufficient informal care in the home situation during the first night following surgery and patients with complaints that necessitate postoperative monitoring (e.g. cardial, pulmonal or neurological diseases) are scheduled for at least one overnight stay. This decision is made in consultation with the anaesthesiologist. The breast nurse scores the reasons for patients who do not participate.

### Informed consent

Eligible patients are informed about the study by the breast nurse during a consultation separate from the consultation in which they are informed about the diagnosis breast cancer. Patients are given an informed consent form by the breast nurse when they are informed about the study, and they are asked to return the signed informed consent within a week. The informed consent regards consent to being asked to complete questionnaires with the aim to evaluate the cost-effectiveness of (the implementation of) the innovative care programme.

### Sample size calculations

In the uhM the percentage of patients discharged within 24 hours has increased from 13% to 84%. Our assumption is that the clinically significant difference of ultra short stay admissions between the pre and post measurement is at least 30% in all participating hospitals. To achieve this percentage, 40 patients are sufficient for both the pre and the post measurement in each of the hospitals to demonstrate statistical relevance (p < 0.05) with a power of 0.90[22].

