## Discussion

Breast cancer surgery on an inpatient basis is a burden on the health care budget. Although previous studies have shown that ambulatory surgery is feasible for breast cancer patients, this has not been widely recognised in Europe. This is, to our knowledge, the first study that systematically evaluates the impact of an implementation strategy on patient and professional outcomes, patient experiences, costs, barriers and facilitators for change, for ultra short stay after breast cancer surgery.

A randomised controlled trial is usually preferred over any other design. However, for several reasons a randomised controlled trial was not regarded as feasible. The first reason concerns the expected lack of willingness on the part of hospitals to be allocated to the control condition as they would get nothing in return for their efforts had we chosen a design with a concurrent control group. The number of participating hospitals in the study is too small to allow a controlled study design. A controlled study would have led to an unacceptable rise in study costs and the study period was too short to construct a waiting list control group. However, we think that the numbers of patients from the four participating hospitals provide enough power to draw conclusions on the estimation of change.

Random allocation at patient level was not considered for legal and organisational reasons; patients always have the right to go home whenever they want, making randomisation for early or late discharge rather meaningless. Moreover, it is unethical to have one patient discharged the day of surgery while her neighbour is allowed to stay for another day or two. The extent of organisational changes to implement short stay within the existing processes of care are of such a scale that it is hardly feasible nor acceptable to allow different admission periods at the same time within one hospital.

We are aware that the decision for a pre-post design instead of a randomised controlled trial cannot rule out the influence of developments and ongoing changes in health care, including reductions in lengths of hospital stays. This aspect will, therefore, be taken into account when conclusions are drawn based on the results of the study.

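### The per-hospital power of 0.90 with 40 patients per period is tied to no baseline or sidedness; two-sided power is about 86–89% at the only baseline quoted and about 78–80% near a 35% baseline

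*Protocol article*

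**What the plan says.** The section on sample size calculations first reports that at the hospital where the programme was developed, discharge within 24 hours rose from 13% to 84%. It then takes as its planning assumption that "the clinically significant difference of ultra short stay admissions between the pre and post measurement is at least 30% in all participating hospitals". From this it concludes that "40 patients are sufficient for both the pre and the post measurement in each of the hospitals". The criterion attached to that number is a p value below 0.05 and 90% power. The abstract gives the same number as a minimum: "in at least 40 patients per hospital per measurement period".

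The section gives no expected baseline for the four test hospitals and does not say whether the test is one- or two-sided. The only support for the calculation is a literature reference. The 13% is not presented as the planning rate for the test hospitals.

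**The concern.** For a fixed absolute difference between two proportions, the variance, and so the power, depends on where the two proportions lie. A single sample size cannot give the same power for a 30-point rise at every starting level. The article nevertheless attaches one power figure to each hospital without a starting level. A two-sided calculation at the only baseline it mentions falls short of 0.90.

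What is at stake is how single hospitals are read. The hospitals were chosen by type so that differences in results might be related to setting. If the true per-hospital power is 78–86% (pooled formula), a hospital that really gains 30 points has a 14–22% chance of a non-significant result, not the 10% implied. Such a result could be taken for failed implementation or for an effect of setting.

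**Working it through.** **Inputs from the protocol article.** n = 40 before and 40 after in each hospital; difference d = 0.30; significance level 0.05; power 0.90 (sample size section). The outcome is binary, and the two periods involve different patients.

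**Inputs that must be assumed.** Sidedness: two-sided first, then one-sided. Baseline p1: 13% (the developing hospital's earlier rate), and 35% as a mid-range value. The 35% is not in the article; it is where a 30-point rise has its largest variance (35% to 65%).

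**Formulas.** Let p2 = p1 + 0.30, p̄ = (p1 + p2)/2 and V = p1(1 − p1) + p2(1 − p2).
- Pooled: power = Φ{[d√n − z_α √(2p̄(1 − p̄))]/√V}, and n for 90% = {[z_α √(2p̄(1 − p̄)) + 1.282√V]/d}².
- Unpooled: power = Φ{d√n/√V − z_α}, and n for 90% = (z_α + 1.282)² V/d².

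z_α is 1.960 two-sided and 1.645 one-sided. d√n = 0.30 × √40 = 1.897.

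**Can the stated 40 be reproduced?** Yes, under particular choices. Two-sided, 40 per period is what the pooled formula requires at an 8% baseline and what the arcsine formula requires at 10%. One-sided at 13%, the pooled formula requires 37, so 40 is enough.

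**13% to 43%, two-sided.** p̄ = 0.28, √(2 × 0.28 × 0.72) = 0.635, V = 0.1131 + 0.2451 = 0.3582, √V = 0.5985.
- Pooled: (1.897 − 1.960 × 0.635)/0.5985 = 1.091, power 86.2%; n for 90% = 45.
- Unpooled: 1.897/0.5985 − 1.960 = 1.210, power 88.7%; n for 90% = 42.

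**35% to 65%, two-sided.** p̄ = 0.50, √(2 × 0.5 × 0.5) = 0.707, V = 0.455, √V = 0.6745.
- Pooled: (1.897 − 1.960 × 0.707)/0.6745 = 0.758, power 77.6%; n for 90% = 57.
- Unpooled: 1.897/0.6745 − 1.960 = 0.853, power 80.3%; n for 90% = 54.

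**Power for a 30-point rise with 40 + 40:**

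| Baseline | Two-sided, pooled | Two-sided, unpooled | One-sided, pooled | One-sided, unpooled |
|---|---|---|---|---|
| 5% | 93.4% | 95.1% | 96.7% | 97.6% |
| 10% | 88.8% | 91.0% | 93.9% | 95.1% |
| 13% | 86.2% | 88.7% | 92.3% | 93.6% |
| 20% | 81.6% | 84.2% | 89.1% | 90.6% |
| 35% | 77.6% | 80.3% | 86.2% | 87.9% |
| 50% | 81.6% | 84.2% | 89.1% | 90.6% |

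Exact two-sided power is 87.1% at 13% and 79.5% at 35% for the chi-square test, and 81.5% and 72.4% for Fisher's test.

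**Where 90% is reached with 40 + 40.**
- Two-sided: baselines up to 8.6% (pooled) or 11.3% (unpooled), and by symmetry from 61.4% or 58.7% upwards.
- One-sided 5%: baselines up to about 18% (pooled) or 22% (unpooled), and from about 52% or 48% upwards.

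**Difference detectable with 90% power, two-sided pooled.** 32 points from 13%, and 35 points from 35%.

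**The case against.** The strongest reply is that no arithmetic error has been proved. The article names neither baseline nor sidedness nor formula, its reference cannot be consulted here, and 40 reproduces under ordinary choices. At 13% the two-sided shortfall is only 1 to 4 points under the normal approximations, and it vanishes for a one-sided test. The article describes ultra short stay as not yet common in Europe, which fits a low baseline better than the assumed 35%. Both inputs are also minima: at least 40 patients per hospital and period, and a rise of at least 30 points. At 13%, 45 patients per period or a 32-point rise restores 90%.

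All of this stands, and it limits the point to a power figure that is fixed without its conditions. It does not rescue the figure as written. No one-sided test is stated, no two-sided calculation tried reaches 90% at 13%, and no variant, one-sided included, reaches it at 35%. A baseline above 13% is an assumption, but not a remote one. The test hospitals are early adopters, and the Discussion acknowledges both ongoing reductions in length of stay and possible contamination of the baseline period.

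A reader might go further and infer from "at least 30% in all participating hospitals" that all four hospitals must be separately significant, and then multiply the four powers. The article sets no such target: that phrase describes the assumed difference, not a joint success rule. A reader might also infer that the study as a whole is underpowered. That does not follow either. Combining the hospitals gives 4 × 40 = 160 patients per period, and 160 against 160 has over 99.9% power for 30 points at either baseline before any allowance for clustering. The Discussion's statement that "the numbers of patients from the four participating hospitals provide enough power to draw conclusions on the estimation of change" appeals to those combined numbers and is not at fault here.

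**Conclusion.** The point holds in a limited form. The per-hospital claim of 0.90 is not secured by 40 patients per period. With a two-sided 5% test, power is about 86–89% at the only quoted baseline and about 78–80% near 35%, and the stated figure fails for every baseline between about 11% and 59% even under the more favourable unpooled formula. These results rest on independent patients in the two periods, exactly 40 per period, a true rise of exactly 30 points and the normal approximation; Fisher's test would give less. The 35% is an assumption, and the shortfall at 13% is small. Severity is moderate to minor: it bears on how single hospitals are interpreted, not on the power of the combined comparison.

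**What to change.** In the sample size section, state the assumed baseline, the sidedness and the formula, and restate the figure accordingly. For example: with 40 patients per period and a two-sided 5% test (normal approximation, pooled variance), power per hospital is about 86% for a rise from 13% to 43% and at least 77% for a 30-point rise from any baseline. Alternatively, keep 90% power and restate the detectable difference as about 32 points from 13% and about 35 points at mid-range. If a one-sided test was intended, say so and give the baselines for which 40 is enough.

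Report each hospital's before–after difference with a 95% confidence interval, so that a non-significant result in one hospital is not read as failed implementation.

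The cost is wording and four intervals in the report. No extra patients are needed; the stated per-hospital power becomes somewhat less favourable.
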